##### Interviews

The structured telephone interview on the implementation of the project comprises both predetermined and open-ended questions, the content of which is based on the planned course of the EXPERT project. For each of the 4 project phases—“Preparation,” “Development of new standards,” “Cooperation with the Extremity Board,” and “Implementation of therapy recommendations”—3 to 5 items were designed in the form of statements, which are assessed by the interviewees based on a 10-point scale. For example, one item regarding the project phase “Preparation” is as follows: “All employees involved in the project were able to obtain sufficient information about the new work steps and tasks, e.g., through training. (1=not true at all, 10=completely true).” An example for the project phase “Collaboration with the Extremity Board” is as follows: “The case presentations in the Extremity Board are helpful for the planning of treatments.”

The open questions of the interview relate to aspects that the interviewees consider to be particularly important for the transfer of the project measures into standard care. The questioning technique used in this study is a simplified modification of the repertory grid technique [58,59]. In total, 2 open-ended questions refer to sequencing of steps within the project: (1) preparation phase, (2) development of new standards, (3) cooperation with the Extremity Board, and (4) implementation of the therapy recommendations. The participants are asked to describe what they like or dislike within the project steps. Regarding the most likeable and the most undesirable aspects, the participants are asked how important these aspects are for the future implementation of an Extremity Board (1=*not important at all*; 10=*very important*). This results in 8 aspects per interview that are relevant for the long-term implementation of the Extremity Board from the point of view of the hospital staff.

### Data Analysis

#### Clinical and Health Economic Evaluation

The eligible patients are enrolled in the project by trained staff. Patients are informed about the objectives and course of the project and give their written consent to participate. Each case is summarized with all relevant information (eg, anamnesis, findings, and imaging) in a clinical case file using data-secure web-based software. The case files are checked for completeness and, after approval, transmitted digitally to the interdisciplinary expert group, the Extremity Board. This group of experts is recruited from the following disciplines: trauma surgery, plastic surgery, vascular surgery, radiology, angiology, and antibiotic stewardship (microbiology, hygiene, infectiology, and pharmacy) [43]. The experts meet at least weekly via web conference and, depending on the urgency, discuss the cases together. Agreed interdisciplinary therapy recommendations are written and transmitted back to the presenting clinic via the web-based software platform. In addition, guidelines will be defined in the course of the project on the basis of the findings gained by the Board to objectify decision-making paths, streamline processes, define therapy algorithms, and enable the supraregional applicability of these standards.

The clinical case files of all patients included in the EXPERT project will be merged with the respective patient-related health insurance data in an anonymized data file for each case while maintaining data protection. Claims data from health insurance companies provide information about the use of health services and the costs that arise in doing so. To obtain information about the individual course of treatment after the introduction of the new form of care, claims data for the following 6 months are included in the evaluation for each patient from the time of enrollment in the sample. Thus, the clinical case file and the associated health insurance data depict the course of treatment of a patient, which is included in the evaluation.

To be able to evaluate the extent to which the new care measures improve the chances of recovery and reduce costs, various clinical and economic outcomes are collected.

First, the primary outcome of the complication rate as well as the secondary and health economic outcomes are evaluated descriptively using absolute and relative frequency distributions as well as position and scattering measures (eg, median, variances, SD, and representation by means of box plots or histograms). The differences between patients in the control and intervention phases are checked using appropriate statistical methods (eg, Mann-Whitney *U* test [60,61], chi-square test, or odds ratio [62]). In addition, individual subgroups (eg, by sex and age) are analyzed to check the data for possible biases.

This descriptive analysis is followed by interference statistical analyses. By means of suitable regression analyses (eg, using generalized linear regression models), it can be examined which regressors have an influence on the primary and secondary outcomes. In addition to the consideration of temporal and intervention-related effects, the influence of potential confounders is also controlled for. This is because various patient- and trauma-associated factors are relevant risk factors for the development of a complication in the treatment of open fractures. For example, male sex, age of >60 years, BMI of >40 kg/m^2^, use of nonsteroidal anti-inflammatory drugs, diabetes mellitus, and nicotine consumption are positively correlated with the development of an infection or fracture healing disorder [63]. This also applies to fractures in the context of multiple injuries (polytrauma) or in the context of agricultural accidents [64,65]. The quality of the statistical models is tested with the help of a residual analysis. Sensitivity analyses are carried out to check the stability of the evaluation and the assumptions made, for instance, the effects of changed influencing variables on the result.

As part of the health economic evaluation, the use as well as the costs of health services and absences from work are considered. For this purpose, a cost-effectiveness analysis is carried out whereby the incremental cost-effectiveness ratio will be calculated. The evaluation of routine statutory health insurance data is carried out according to the principles of good secondary data analysis [66], the recommendations of the “Methods for Health Services Research” memorandum [67], and the standards of the German Evaluation Society [68]. The data basis for the evaluation comprises the statutory health insurance routine data, the data from the case file, and the collected data on the health economic quality of life.

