## Abstract

**Background:**

Patients with open fractures often experience complications during their injury. The treatments incur high costs. Interdisciplinary cooperation between different medical disciplines may improve treatment outcomes. Such cooperation has not yet been envisaged in the German health care system.

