### Outcomes and Measures

#### Clinical and Health Economic Evaluation

The primary outcome and various secondary clinical outcomes are recorded based on data from the clinical case file as well as routine data from the health insurance companies.

The primary clinical outcome is the complication rate of open fractures or the occurrence of postoperative complications, which is collectively defined as a dichotomous outcome. Either the occurrence or nonoccurrence of complications is observed. The following events are complications if they occur within 6 months of enrollment in the sample: (1) occurrence of pseudarthrosis (incomplete fracture healing; *ICD-10* code M96.0); (2) occurrence of chronic osteomyelitis (*ICD-10* code M86.69); (3) unplanned follow-up procedures, such as wound revisions and Negative Pressure Wound Therapy (*ICD-10* code S81.801); (4) deviation from standardized antibiotic therapy (extension of the duration of therapy or change or expansion of the active substance; *ICD-10* code T36.95); (5) occurrence of antibiotic-associated complications (eg, clostridia infection or allergy; *ICD-10* code B96.7); (6) infection with resistant germs (eg, methicillin-resistant *Staphylococcus aureus*) that occurred during inpatient treatment and did not exist at the time of trauma (*ICD-10* code A49.02); (7) need for unplanned inpatient treatment; and (8) death of the patient related to the trauma (not due to other causes).

Secondary clinical outcomes include the number of antibiotics administered, limb function, and health-related quality of life (HRQoL) [44,45].

Health economic outcomes are mapped through claims data from health insurance companies. These will be recorded for each patient included in the project up to 6 months after enrollment in the sample. Specifically, the following features will be recorded: (1) use of health services (eg, contact with physicians and therapists, operations, and inpatient stays), (2) cost of health care services (inpatient hospital costs, outpatient costs, rehabilitation costs, medical and medical aid costs, drug costs, and total costs), (3) number of days on which there is incapacity for work, and (4) number of days on which sickness benefits are received.

Table 1 provides an overview of the clinical and health economic outcomes used in this study.

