## Discussion

### Principal Findings

The aim of the EXPERT project is to improve the treatment of fractures with open soft tissue damage or postoperative complications rapidly and sustainably. To perform optimized multifaceted treatment, we consider the following disciplines an essential part of the interdisciplinary team: trauma surgeons, vascular surgeons, plastic surgeons, specialists for infectious diseases, radiologists, pharmacologists, hygienists, and microbiologists. We think that an interdisciplinary board needs several disciplines to not only enable a complete interdisciplinary treatment approach but also develop interdisciplinary treatment algorithms for infections or provide interdisciplinary prophylaxis in musculoskeletal surgery.

In addition to the evaluation of the clinical outcome, the cost reduction and cost-effectiveness of the new intervention will be evaluated based on claims data provided by 3 major statutory health insurance companies. The focus will be on use of health services and their cost as well as the duration of incapacity for work and HRQoL.

Furthermore, a process evaluation will explore the impact on workload, job satisfaction, and technology acceptance throughout the implementation phase and individual onboarding processes of the caretakers.

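### The incremental cost-effectiveness ratio has no listed cost item for the Extremity Board itself, so unless Board cases are paid through claims it is biased in the Board's favour

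*Protocol article*

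**What the plan says.** The Data Analysis section (Clinical and Health Economic Evaluation) commits to the measure: "a cost-effectiveness analysis is carried out whereby the incremental cost-effectiveness ratio will be calculated". It then names the inputs: "The data basis for the evaluation comprises the statutory health insurance routine data, the data from the case file", together with quality-of-life data.

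Three other places describe the cost side in the same way:

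- Outcomes and Measures: "Health economic outcomes are mapped through claims data from health insurance companies". The itemised list there reads "cost of health care services (inpatient hospital costs, outpatient costs, rehabilitation costs, medical and medical aid costs, drug costs, and total costs".
- Table 1 gives claims data as the only source for every health economic outcome.
- Discussion, Principal Findings: "the cost reduction and cost-effectiveness of the new intervention will be evaluated based on claims data provided by 3 major statutory health insurance companies".

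The article also describes what the intervention consumes. The Data Analysis section says "The experts meet at least weekly via web conference and, depending on the urgency, discuss the cases together". It adds completeness checks of case files, written recommendations and a web-based platform. Study Design describes a transition phase used for implementation, testing and staff training. The Abstract says of this kind of interdisciplinary cooperation: "Such cooperation has not yet been envisaged in the German health care system".

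**The concern.** A cost-effectiveness ratio compares the full cost of two ways of providing care, including the cost of providing the new one. Here the article lists the data sources and cost items, and the list covers only the care that patients receive. The Board's experts, the platform, the training and any extra work at the presenting clinic have no item and no data source. These resources are used only or mainly on the intervention side, so leaving them out does not cancel between the phases.

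The article itself expects extra burden. Its hypothesis 1a predicts that workload rises in the intervention phase, but this is measured on rating scales and given no money value.

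The use of the result is at stake. Cost-effectiveness is to be evaluated, and the interviews ask staff what matters for transfer into standard care. A ratio without the Board's cost cannot show whether the Board pays for itself once someone has to fund it.

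**Working it through.** The article gives no ratio, no Board cost and no expected cost difference, so there is no stated figure to reproduce. The check has three steps.

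**1. Is there a place for the intervention's cost?**

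| Resource described | Where described | Cost item or data source named |
|---|---|---|
| Expert time, at least weekly conference | Data Analysis | None |
| Case preparation and checking | Data Analysis | None (case file gives content, no unit cost) |
| Web-based platform | Objectives; Data Analysis | None |
| Training and implementation | Study Design | None |

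A route through claims is possible only if insurers pay for Board cases as a claim. The article does not say that they do.

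**2. Effect on the ratio.** The inputs from Data Sampling are a complication rate of 40% under control and 30% under the intervention. The article does not fix the effect measure of the ratio, so I assume complications avoided. If a cost C per intervention-phase patient is left out, the ratio is too low by

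C / (0.40 − 0.30) = C / 0.10 = 10 × C per complication avoided.

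| C, assumed (EUR per patient) | Ratio too low by (EUR per complication avoided) | Omitted over the 1428 planned intervention-phase patients (EUR) |
|---|---|---|
| 100 | 1,000 | 142,800 |
| 250 | 2,500 | 357,000 |
| 500 | 5,000 | 714,000 |
| 1,000 | 10,000 | 1,428,000 |
| 2,000 | 20,000 | 2,856,000 |

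With another effect measure the divisor changes. If the intervention is beneficial on that measure, the direction of the bias does not.

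**3. Is the omission large against the possible saving?** Both sides need assumptions.

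Board cost per case, assuming 6 to 10 experts, 10 to 20 minutes per case, EUR 60 to 100 per hour and 30 to 60 minutes of case preparation, before platform and training:

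- Low: 6 × (10/60) × 60 + 0.5 × 60 = 60 + 30 = EUR 90.
- High: 10 × (20/60) × 100 + 1 × 100 = 333 + 100 = EUR 433.

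Case files are kept for all patients, so part of the preparation may not be incremental. Expert time alone is EUR 60 to 333.

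Saving per patient = 0.10 × cost of a complication:

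- The Introduction gives EUR 11,000 for open and EUR 6,600 for closed lower-leg fractures. The difference, EUR 4,400, is an imperfect proxy for the cost of a complication. Saving: 0.10 × 4,400 = EUR 440. The omitted EUR 90 to 433 is 20% to 98% of it.
- The Introduction also says infection can raise costs 6-fold. Applied to EUR 11,000, the extra cost is 5 × 11,000 = EUR 55,000. Saving: EUR 5,500. The omitted cost is then 2% to 8% of it.
- The composite also counts antibiotic changes and wound revisions, so an average complication may cost less than either figure.

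Platform and training are largely fixed, so their share per case rises if volume is low. The article reports 425 patients included by 13 June 2024, against 3366 planned.

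**The case against.** The strongest reply is that the exclusion is inferred. No sentence says that Board costs are left out or set to zero. The article gives the economic analysis one short paragraph, and a fuller health economic plan may contain a costing. The listed data basis can be read as patient-level sources only, with unit costs added elsewhere. The case file could supply counts of Board presentations, and sensitivity analyses on assumptions are planned. Three statutory insurers are consortium partners, and the article is silent on whether they pay for Board cases. That such cooperation is not yet part of German care in general does not settle how it is paid for within this project.

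Most of this stands, and it limits the point to a conditional one. It does not remove it. The article goes beyond silence: it names the measure, the sources and the cost items, and the Discussion again ties cost-effectiveness to claims. Counts of presentations without a unit cost do not produce an intervention cost.

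A reader might infer three stronger things that the documents do not support:

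- **That the plan treats the Board as free.** This would follow only if nothing is reimbursed through claims and no costing is added elsewhere.
- **That the whole cost objective fails.** The stated aim is to reduce treatment costs, and claims answer that from the payer's side.
- **That the Board's cost would turn a saving into a loss.** With the EUR 4,400 proxy, even the upper EUR 433 stays below EUR 440 before platform and training. A clear reversal needs a lower figure, such as EUR 2,000 per complication (saving EUR 200), which the documents do not give.

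**Conclusion.** The point holds in conditional form. As written, the ratio has no term for the intervention's own cost. Unless Board cases are reimbursed through claims, it is biased in one direction, by EUR 10 per complication avoided for each uncounted EUR 1 per patient. That factor rests on the planned 10-point reduction and on complications avoided as the effect measure. Whether the omission is small or decisive cannot be settled from the documents, since it ranges from a few per cent to nearly all of the illustrative saving.

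This should be fixed, but it affects only the cost-effectiveness conclusion. The primary outcome, the other clinical outcomes and the claims-based expenditure comparison are not touched.

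**What to change.** In the health economic parts of Outcomes and Measures and of Data Analysis:

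1. State the perspective, and say whether Board cases are reimbursed through claims.
2. Add an intervention-cost term for each intervention-phase patient: expert minutes per case (number present × duration), incremental clinic time, and a per-case share of platform and training cost, valued at standard wage rates and from project accounts. Exclude research-only costs and anything already reimbursed in claims.
3. Base the ratio on claims cost plus this term, with a sensitivity range for Board volume.
4. Report the claims-only difference separately, labelled as the change in insurer expenditure excluding the Board.

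The cost is a short time log, best kept while Board sessions are running, project accounting data and one added term in the analysis. No extra patient contact is needed. The downside is a less favourable stated ratio.

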#### Work-Related Evaluation

The original item scaling of all 4 or 5 surveys respectively was retained, and all items were compiled into 1 questionnaire. In total, 4 versions of this questionnaire were created, which are identical in content but have been—with relation to the instructions—slightly adapted to the group (treatment group vs control group) and the time of measurement (before vs after the implementation of the new measures). For example, the instruction before treatment reads “Dear participant,...the clinic where you work...will soon start implementing the new measures” (treatment group) and “...will start implementing the new measures in the foreseeable future” (control group), whereas the instruction in the treatment group after implementing the new measures is “Dear participant,...the clinic where you work...is already implementing the new measures.” The questionnaire was implemented, and postcards with a brief explanation and a QR code with a link to each specific questionnaire version were prepared. Interview guidelines and protocol sheets for the semistructured interview were created, and several fact sheets were written to inform the employees about the interview and data protection aspects.

In the practical implementation of ergonomic data collection, the project staff at Steinbeis University are supported by project staff from University Hospital Münster (Universitätsklinikum Münster [UKM]). Project staff from UKM have contact with the clinics and recruit people there to take part in the questionnaire surveys and interviews.

Before the clinics of cohort 1 start implementing the new form of care in project month 7 (Figure 2), both the clinic staff of cohort 1 (treatment group) and the clinic staff of cohort 3 (control group) will be examined with the EXPERT questionnaire in project months 4 and 5 (measurement time Pre). In project months 12 and 13, clinic staff from both cohorts will repeat the questionnaire (measurement time Post). The same procedure will be followed for cohort 2 and cohort 4, 3 and 9 months later, respectively. Project staff from UKM will recruit enough people in the individual clinics for the surveys. Interested employees in the clinics who are or will be involved in the project can find out more about the survey in advance by means of an information text. The UKM project staff receive a questionnaire link as a QR code from the Steinbeis project staff for the corresponding measurement time tailored to the corresponding group and cohort and send this QR code to a contact person in the clinics. The contact persons pass on the QR code to the participants, who scan it on their mobile phones and answer the questions. Participants are requested to do so as soon as possible after receiving the link. The completed questionnaires are automatically stored anonymously on the Steinbeis University server and later evaluated in summary form.

The UKM staff draw attention to the project-related interviews in the clinics that are already implementing the measures. Interested employees can find out more about the interviews by means of an information text and can contact the Steinbeis project staff to make an appointment for the telephone interview. They then receive an email from Steinbeis with the confirmation of the appointment, the interview questions, and the (renewed) promise that their email address and telephone number will be deleted after completion of the project. The transcripts of the telephone interviews are anonymized using a code. The content collected in the interviews will be evaluated in summary form, quantitatively, and qualitatively.

Regarding the topics of workload, work engagement, work-related resources, and readiness for technology, the main effects and interactions between measurement time (before vs after start of the Extremity Board) and group of measures (treatment vs control) are examined via variance analysis; the result is a 2 × 2 design with the factors time (before vs after) and group (treatment vs control group).

Ergonomic aspects of the telemedicine technology are collected and descriptively evaluated at the second measurement point in approximately half of the clinics.

As staff turnover in hospitals is high, it can be assumed that the groups of employees will be composed differently at each time of measurement. Therefore, no repeated-measure design can be applied. The analyses will be performed as balanced grouping factors with the same number of participants in all conditions (before vs after and treatment vs control). The measurements are considered as a grouping factor of a multiple ANOVA.

The evaluation of the repertory grids yields 2D representations of the negative and positive constructs mentioned by the interviewees during the interviews with respect to the different implementation steps, namely, preparation, development of new standards, interdisciplinary collaboration, and therapy implementation.

The combination of a questionnaire that can be used quickly and easily on a mobile phone and a telephone interview with both predetermined, scaled questions and open-ended evaluations according to the repertory grid technique results in a comprehensive picture of changes in pretest-posttest working conditions and of the success factors accompanying the process both in quantitative and qualitative terms. On the one hand, the web-based questionnaire before and after the introduction of the new form of care quantitatively captures influences on workload, work engagement, work-related resources, and readiness for technology and backs them up through the “difference-in-difference” design. On the other hand, central success factors regarding project implementation will be collected both quantitatively and qualitatively and made visible by means of the repertory grid technology as “mental maps” of the employees in the 31 participating clinics.

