#### Work-Related Evaluation

Physicians and nurses who are or will be involved with the project take part in the work-related evaluation. With medium to small effect sizes (η^2^>0.05 and <0.15), a type-1 error (α) of 5%, and a type-2 error (β) of 20% (80% power), a minimum number of 120 people per measurement point is required for the work- and project-related evaluation (60 people each in the control and treatment groups). A total of 4 employees per clinic at measurement time t0 and 4 employees at measurement time t1 are included in the sample. This results in 31 × 8 = 248 elevations. Care is taken to interview physicians and nurses in equal parts, all of whom are or will be involved in the project measures.

Regarding the interviews for the assessment of the objectives and project implementation, 2 persons from the nursing service and 2 persons from the medical profession are to be interviewed at time t1 in the clinics that are already implementing the new form of care. Approximately 72 people from at least 18 clinics will take part in the interviews.

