Work resources are measured using the German-language questionnaire on resources and requirements in the world of work [54]. For the EXPERT project, 11 items are used, which relate to the resources “Leadership Support,” “Feedback,” “Peer-Support,” “Transparency,” “Diversity,” “Meaningfulness,” “Role Clarity,” “Learning Opportunity,” “Knowledge Management,” “Team Atmosphere,” and “Qualification.” All items are formulated as statements (eg, “I will be informed about all important content when implementing the new measures” [“transparency” resource]), which are rated on a scale from 1 to 6 (1=*not at all true*; 6=*completely true*).

Affinity for technology is measured using the German-language short scale for measuring readiness for technology [55]. It is a questionnaire with 12 items in the 3 scales “TB acceptance,” “TB control belief,” and “TB competence,” of which 9 items are used in this study. The item formulations have been adapted to the EXPERT project (eg, “I am very interested in the new telemedicine application” [acceptance scale], “It essentially depends on me whether I am successful in using the new telemedicine application” [control conviction scale], and “For me, dealing with technical innovations is usually too much to handle” [competence scale]).

The software ergonomics of the new telemedicine application are assessed using the German-language questionnaire Norm of the International Standard Organization 9241/10 [56,57]. On the basis of this instrument, software is evaluated regarding “adaptivity to requirements,” “comprehensibility,” “task appropriateness,” “ability to describe itself,” “fault tolerance,” “individualizable,” and “learning conduciveness.” The assessment of the 7 items is made on a bipolar scale based on symbols (from “– – –” to “+++”).

Finally, employees provide information about their profession (physician or nurse), whether they hold a management position (yes or no), and whether they already had experience in the use of telemedicine before the EXPERT project (yes or no).

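### The staff-survey model has only time and group, so a change in respondent mix that differs between treatment and control clinics would enter the difference-in-difference, although three relevant characteristics are recorded

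*Protocol article*

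**What the plan says.** In the protocol article, Data Analysis, Work-Related Evaluation, the four survey topics are analysed by analysis of variance, and "the result is a 2 × 2 design with the factors time (before vs after) and group (treatment vs control group"). The same section says of the respondents that, because of staff turnover, "it can be assumed that the groups of employees will be composed differently at each time of measurement". It concludes "Therefore, no repeated-measure design can be applied" and continues: "The analyses will be performed as balanced grouping factors with the same number of participants in all conditions". Wave is then treated as a between-person factor: "The measurements are considered as a grouping factor of a multiple ANOVA". No covariate is named.

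Under Outcomes and Measures, Questionnaires, "employees provide information about their profession (physician or nurse), whether they hold a management position (yes or no"), and also whether they had used telemedicine before the project. Under Data Sampling, Work-Related Evaluation, four employees per clinic are planned at each of t0 and t1, and "Care is taken to interview physicians and nurses in equal parts".

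Under Study Design, Work-Related Evaluation, cohorts 1 and 2 are the treatment group and cohorts 3 and 4 the control group, and the difference-in-difference is said to allow a causal interpretation. Strengths and Limitations says the design removes confounding, but adds that it depends on parallel slopes, which may not hold.

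**The concern.** With different people at each wave, the difference-in-difference compares four separate samples. It isolates the intervention only if the mix of respondents changes in the same way in both groups. The article expects the mix to change, and its stated response is equal cell sizes. Equal numbers do not make the samples alike in composition.

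A change in one group only is plausible. Hospitals are randomised to cohorts, but respondents are interested employees who receive a QR code through a clinic contact person. At the Post wave, treatment clinics already work with the Extremity Board and control clinics do not, so the pool of involved and interested staff may have moved in one group only. If the treated Post wave drew more staff with earlier telemedicine experience, the stated model could report this as the project raising readiness for technology. Technical competence, one of the readiness scales, is the subject of hypothesis 1c.

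The clinical evaluation in the same article does plan control of potential confounders. For the staff survey, the relevant characteristics are collected but not used.

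**Working it through.** **1. The plan's own figures.** Data Sampling gives α = 5%, power 80%, η² between 0.05 and 0.15, at least 120 people per measurement point (60 per group), and 31 × 8 = 248 responses in all. A noncentral F calculation for a one-degree-of-freedom effect, with λ = N·η²/(1 − η²), needs N = 152 at η² = 0.05 and N = 47 at η² = 0.15. N = 120 gives 80% power at η² ≈ 0.062, inside the stated range. Neither 120 nor 248 is in dispute.

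**2. Standard error of the difference-in-difference.** With 60 respondents in each of four cells and a within-cell SD of 1:

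SE = √(4/60) = 0.258 SD.

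Clustering by clinic is ignored here, so the rates below are approximate.

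**3. False effect.** Let g be the difference in outcome between staff with and without a characteristic, in SD. Let Δ be the change in its share in the treatment group minus the change in the control group. The unadjusted estimate is then off by g × Δ. The documents give neither g nor Δ, so both are assumed. The rejection rate of a two-sided 5% test when the true effect is zero is Φ(−1.96 + b/SE) + Φ(−1.96 − b/SE), with b = g × Δ.

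| g (assumed) | Δ (assumed) | False effect b | Rejection rate |
|---|---|---|---|
| 0.5 SD | 20 points | 0.10 SD | 6.7% |
| 0.5 SD | 30 points | 0.15 SD | 8.9% |
| 0.8 SD | 20 points | 0.16 SD | 9.5% |
| 0.8 SD | 30 points | 0.24 SD | 15.3% |

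**4. Simulation.** 5000 runs per case, 62 per cell (248/4), true effect zero:

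| Change in share | g | Unadjusted bias; rejection | Covariate added |
|---|---|---|---|
| 30% to 50% in both groups | 0.5 SD | 0.00; 4.5% | 0.00; 4.5% |
| Stable difference, 20% against 40% | 0.5 SD | 0.00; 5.4% | 0.00; 5.3% |
| 30% to 50%, treatment only | 0.5 SD | 0.10; 6.9% | 0.00; 5.1% |
| 30% to 60%, treatment only | 0.8 SD | 0.24; 14.5% | 0.00; 4.9% |

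Only a differential change causes bias, and adding the covariate removes it.

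**5. Scale.** For a balanced 2 × 2 interaction, f = √(η²/(1 − η²)) and the difference-in-difference is 4f. At the lower bound, η² = 0.05, f = √(0.05/0.95) = 0.229, so the effect is 4 × 0.229 ≈ 0.92 SD. The assumed false effects are 0.10/0.92 ≈ 11% to 0.24/0.92 ≈ 26% of that.

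**6. Precision.** If all 240 responses (4 × 60) are used and η² = 0.05, unadjusted power is already 94%. Covariates explaining 10% to 25% of the variance (assumed) raise it to 96% to 98%, a gain of 2 to 4 points.

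**The case against.** The strongest case on the other side has five parts.

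- **A condensed article may leave covariates to an analysis plan.** Nothing here says they are excluded, so a reader should not infer that adjustment has been ruled out. But the article does name the factors of the model and does state confounder control for the clinical outcomes. The model as written can fairly be taken at its word.
- **Not every difference in who answers matters.** A reader might infer that any change in respondents between waves biases the result. That is wrong: stable differences and common shifts cancel. The article expects turnover in hospitals generally and gives no reason why it should differ by group. This limits the point to differential change.
- **Randomisation of hospitals.** Chance imbalance in staff mix is part of sampling error and does not inflate the type I error. With 60 per cell and a share of 50%, the chance SD of the differential share is √(4 × 0.25/60) ≈ 0.13, and the unadjusted error term already carries it. The raised rejection rates need a systematic shift. Selection of respondents after implementation could produce one, but no shift of that size is documented.
- **Profession is handled in recruitment.** If equal parts are achieved in every cell, profession cannot bias the estimate. This stands as partial protection. It is a recruitment aim carried out through clinic contacts, and nothing comparable covers management position or telemedicine experience.
- **The causal reading is qualified.** Strengths and Limitations concedes that parallel slopes may fail, and a differential change in composition is one way for that to happen. The qualification is partial, because the same paragraph says the design eliminates confounding.

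**Conclusion.** The point holds in limited form. The stated model leaves the difference-in-difference open to any change in respondent mix that differs between treatment and control clinics, while the article expects the mix to change and reads the result as causal. Under assumed differential shifts of 20 to 30 points and assumed covariate effects of 0.5 to 0.8 SD, the false effect is 0.10 to 0.24 SD and a nominal 5% test rejects in about 7% to 15% of cases.

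A reader might go further and infer that the survey result will be biased, or that composition alone could produce the planned effect. The documents support neither. They report no differential shift, and the assumed bias is about a quarter or less of the 0.92 SD implied by η² = 0.05. The gain in precision is secondary and probably small. The survey is separate from the primary clinical outcome, so this is a worthwhile improvement and does not threaten the trial's main conclusion.

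**What to change.** In Data Analysis, Work-Related Evaluation, keep the time, group and time-by-group terms and add profession, management position and telemedicine experience before the project as covariates. Name the adjusted time-by-group effect as the difference-in-difference estimate. Tabulate the three characteristics in each of the four cells, so that readers can see whether the mix changed differently in the two groups and whether the equal-parts aim was met.

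The cost is about three degrees of freedom out of roughly 240, and no new data. Telemedicine experience is asked as it stood before the project, so the intervention cannot have altered it and adjusting for it is safe. When the article was written, 146 people had taken part in the survey against 248 planned responses, so the model could still be settled before data collection was complete. Adjustment covers only these three characteristics. Changes in unmeasured ones would remain, and the causal wording should say so.
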